#### Statistical analyses

All data will be entered into a customized Access database (Microsoft, Redmond, Wash, USA). Analyses will be performed using Stata, version 12. All data will be analyzed by intention to treat. The tests were two-sided, with a type I error set at α = 0.05 (except for multiple comparisons when appropriate). Baseline characteristics (GPs and their patients) will be presented as the mean ± standard deviation (SD) or the median (interquartile range) for each randomization group for continuous data and as the number of patients and associated percentages for categorical parameters. Hierarchical linear regression models (mixed models) with levels for practice, individuals within practices, and repeated measurements per individual have been used to estimate effects of the intervention on number of joints smoked per month post-baseline time points. These models (intercept and slope as random effects) included an interaction between randomization group and time point, and adjusted for number of joints smoked per month at baseline, age of first consumption, gender, CAST at baseline, socioeconomic status, and GP’s characteristics. Intraclass correlation coefficients are presented by arm. The secondary analyses will compare changes on between groups with random effects models: method of consumption, supply method, perception of the effects on health, professional life, social life, and driving under the influence of alcohol will be also compared. This data will be collected through a self-administered questionnaire that the patient will complete and leave at the GP’s surgery. To assess the problem caused by missing data (GP and patients), estimation methods developed by Verbeke and Molenberg are proposed.

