## Methods

The main assessment criterion is the amount of joints consumed per month at the 12^th^ month following the inclusion consultation. In the absence of consensus on the definition of a threshold for dangerous cannabis consumption, it is impossible to refer to a target level of consumption. In the light of epidemiological data (proportions of recent, repeated, regular, and daily users in the age group 15–25 years) [1,2], we considered that cannabis users consumed an average of 15 joints per month. Our working hypothesis is that the intervention will result in a 30% reduction in the stated consumption of cannabis at 12 months (that is to say five joints per month). The Hawthorne effect [24] was taken into account by estimating that adolescents of the control group would reduce their consumption by 15% (i.e., two joints per month).

A difference of 30% between the intervention group (i.e., three joints per month) and the control group appears to be clinically relevant.

Some secondary hypotheses are reported in case report forms (CRFs) at 3, 6, and 12 months by the GP: the change to other methods of cannabis consumption such as consumption by “bong” or “water pipe” and the impact of the change in cannabis use on tobacco and alcohol consumption.

Other secondary hypotheses are collected by a declaratory self-administered questionnaire completed by the patient at the start and end of the study: how it is consumed (alone or with friends, weekday or weekend, joints or bongs), changing perceptions of the danger of consumption for health, and driving after smoking.

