### Recruitment

In both groups, the investigators identify eligible adolescents who consume cannabis by asking them the following questions: “Do you smoke cannabis? For how long have you smoked it? How much do you smoke?” The volunteer GPs recruit the first five eligible adolescents that they consult, regardless of the reason for their consultation. Participation requires a prior consent, a guarantee of anonymity, and an unconditional right to withdraw.

During this consultation, the investigators of the intervention group conduct an interview using the BI technique with the eligible and voluntary adolescents.

The doctors of the two groups provide the patient with an anonymous self-administered questionnaire to complete during the consultation. This self-administered questionnaire makes it possible to collect additional information such as method and times of consumption, monthly cost of consumption, and a cannabis abuse screening trial (CAST) score. The self-administered questionnaire is used in order to not influence the course of the consultation with adolescents of the control group and reduce the Hawthorne effect.

During the follow-up consultation at 3 and 6 months, the main assessment criterion is specified as well as cigarette and alcohol consumption. The investigators of the intervention group carry out a BI at each consultation. During the final consultation at 12 months, the doctors of the two groups provide another self-administered questionnaire.

If the adolescent does not attend the following consultation, the doctor can contact him/her by phone to make another appointment or at least to obtain the required data. To help investigators, the coordinators send a schedule of the consultations expected for each patient, as well as reminders to the GPs.

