### Statistical considerations

#### Sample size estimation

The calculation of the necessary amount of adolescents was carried out on the basis of a variation in consumption between the randomization groups of the amount of joints at 1 year, based on data from literature relating to the effect of a BI on alcohol consumption [10]. Given that the published data has heterogeneous values in terms of standard deviation associated with the quantity of joints consumed and considering the importance of a possible declarative bias, various simulations were carried out according to the value of this standard deviation (s = 1.5, 2, 3, 4 and 5) for 90% power and 5% two-sided type 1 error taking into account inclusion of five patients per GP, clustering by practice (intra-cluster correlation considered between 0.05 to 0.20 [25,26], a 10% dropout rate of GP and 20% of patients [27]). By considering the results of these simulations, a minimum of 250 patients is required to highlight a relative variation in the reduction in consumption of the amount of joints of 50% between the two groups (30% vs. 15%). This represents 50 investigators (25 in each randomization group). This design is respected in each region for an analysis stratified by region and thus highlights a variation per region. In total, 150 investigators (50 per region) must include 750 patients.

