## Discussion

The main assessment criterion being consumption by amount of joints smoked in each group, it is difficult to establish a quantity of consumption for cannabis (e.g., shared joints, joints that are more or less 'concentrated’). The epidemiologic data usually quantifies consumption by 'use’ of cannabis: that is to say 'the amount of times that the adolescent has smoked’ [1,3,4]. Concordances were established; half of recent smokers smoke one or less than one joint per use, and 70% of them smoke two or less. Regular or occasional smokers smoke five joints or more per use in 30% of cases [4]. It would have been possible to assess consumption more objectively using biological sampling (hair samples, urine tests). However, early treatment in general medicine requires a relationship of trust between the doctor and the patient; mandatory biological testing would have been badly received by adolescents. The CAST score (Cannabis Abuse Screening Test) is only assessed at the start of the study, as it has the sole objective of detecting problematic use of cannabis [28,29], but is not suited to measuring the progression of consumption. It will enable comparison of the progression of consumption in adolescents who had an initial score which revealed harmful use and the others. The primary and secondary criteria are collected during the preceding month, then at 3, 6, and 12 months. Collection during the preceding month was chosen in order to limit memorization bias, while maintaining a sense of overall consumption, as certain patients do not consume cannabis regularly.

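### The primary model, as written, shares one baseline-joints coefficient across months 3, 6 and 12; a baseline-by-time-point term would be a nearly free safeguard for the 12-month contrast (minor)

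*Protocol article*

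**What the plan says.** All references are to the protocol article.

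- **Endpoint** (Methods): "The main assessment criterion is the amount of joints consumed per month", measured 12 months after the inclusion consultation.
- **Visits** (Discussion): "The primary and secondary criteria are collected during the preceding month, then at 3, 6, and 12 months".
- **Structure of the model** (Statistical analyses): a hierarchical linear model with "levels for practice, individuals within practices, and repeated measurements per individual", fitted to the post-baseline visits, with a random intercept and slope.
- **Fixed effects** (same section): the models "included an interaction between randomization group and time point, and adjusted for number of joints smoked per month at baseline". Baseline joints heads a list of adjustment covariates that also holds age of first consumption, gender, baseline CAST, socioeconomic status and GP characteristics. Group by time point is the only interaction named.
- **Recruitment**: surgeries are the unit of randomisation (Randomization), and patients come in afterwards: "The volunteer GPs recruit the first five eligible adolescents that they consult".

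**The concern.** The group effect may differ at each visit, but the coefficient that corrects it for baseline consumption may not. A baseline measurement often predicts the next visit better than one a year later. If that happens here, the shared coefficient is too steep at month 12, the one visit that carries the primary criterion. A baseline difference would then be over-corrected. The intervention would look better than it is if its arm started heavier, and worse if it started lighter.

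The trial's own hypothesis gives a second reason why the coefficient might move. Proportional reductions of 30% and 15% change the slope on baseline. If they build up linearly over the year (an assumption), the arm-averaged slope is 1 − 0.225 × t/12, which is about 0.94, 0.89 and 0.78 at months 3, 6 and 12. If the full reduction is reached by month 3 and holds, this reason disappears.

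The random intercept and slope do not help. They describe the covariance. When variance grows with time, they shift the estimation of the shared coefficient towards the early visits.

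**Working it through.** The document states no figure on this point, so there is none to reproduce. The sample size of 250 per region does not enter.

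**Inputs from the document.** Mean consumption 15 joints per month; reductions of 30% and 15%; largest SD considered 5; upper ICC 0.20; 5 patients per GP; 25 GPs per arm in each of three regions. The planned gap is 15 × (0.30 − 0.15) = 2.25 joints. Methods rounds it to three.

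**Assumed inputs.** The baseline coefficients at months 3, 6 and 12 (b3, b6, b12) and the residual covariance V. The document gives neither.

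**1. Formula.** With group by time point saturated and complete data, the estimated 12-month effect is the difference in 12-month means minus b × D. D is the baseline difference (intervention minus control). The shared coefficient b is the weighted mean of b3, b6 and b12, with weights w = V⁻¹1 / (1′V⁻¹1). The error given D is therefore (b12 − b) × D.

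**2. Weights.** Take a patient intercept SD of 4, slope SD of 0.4 per month and error SD of 4. The residual variances at the three visits are then 33.4, 37.8 and 55.0, and the weights are 0.53, 0.38 and 0.09. With a random intercept only, each visit has weight 1/3. The random slope thus moves weight away from month 12.

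**3. Error per joint of baseline difference.** With coefficients 0.8, 0.7 and 0.5:
- random intercept and slope: b = 0.736, so the error is 0.5 − 0.736 = −0.24;
- equal weights: b = 0.667, so the error is −0.17.

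Over a range of covariances:

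| Assumed b3 / b6 / b12 | Error per joint |
|---|---|
| 0.6 / 0.6 / 0.6 | 0 |
| 0.7 / 0.65 / 0.55 | −0.08 to −0.15 |
| 0.8 / 0.7 / 0.5 | −0.17 to −0.31 |
| 0.9 / 0.7 / 0.3 | −0.33 to −0.61 |

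**4. Chance baseline difference.** The design effect is 1 + 4 × 0.2 = 1.8.
- Whole trial, 375 per arm: SE = √(2 × 25 × 1.8 / 375) = 0.49 joints.
- One region, 125 per arm: SE = √(2 × 25 × 1.8 / 125) = 0.85 joints.

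**5. Size of the error** for a one-SE difference and coefficients 0.8, 0.7 and 0.5.
- Whole trial: 0.49 × (0.17 to 0.31) = 0.08 to 0.15 joints, or 4% to 7% of 2.25.
- One region: 0.85 × (0.17 to 0.31) = 0.14 to 0.26 joints, or 6% to 12% of 2.25.
- The SE scales with the SD. At an SD of 15 to 25 (assumed), the whole-trial SE is about 1.5 to 2.4 joints and the error about 0.25 to 0.75.

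**6. Simulation** (1,500 trials per scenario, 75 GPs per arm, SD 5, ICC 0.2, complete data). Entries are the mean error of the 12-month estimate; the Monte Carlo SE is about 0.01.

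| Coefficients, systematic difference | Shared coefficient | Visit-specific coefficient |
|---|---|---|
| 0.8/0.7/0.5, none | 0.016 | 0.019 |
| 0.8/0.7/0.5, 1 joint | −0.219 | 0.013 |
| 0.6/0.6/0.6, 1 joint | 0.005 | 0.006 |

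With no systematic difference, the SD of the estimate is 0.401 (shared) against 0.387 (visit-specific) for coefficients 0.8, 0.7 and 0.5. It is 0.393 under both models when the coefficients are equal.

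**The case against.** A reader might infer that the primary analysis is biased whenever the arms differ at baseline. The documents do not support that. The coefficient must also change over visits; with equal coefficients the error is zero for any baseline difference. No correlation between baseline and follow-up is given, so the weakening is a plausible assumption and no more. A chance imbalance does not bias the estimator, because its error averages out over randomisation.

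A systematic difference is possible, since intervention GPs are trained and deliver the intervention at the inclusion consultation, so they recruit knowing their arm. It is not shown, however. Both arms use the same screening questions and the same consecutive-recruitment rule. If selective recruitment did occur, patients could also differ in unmeasured ways that this term would not correct. That the planned losses ("a 10% dropout rate of GP and 20% of patients") would widen the difference is likewise conjecture.

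It can also be said that an article's covariate list does not rule out a visit-specific coefficient, and that such detail belongs in the full analysis plan. This has weight, and a fuller plan may already contain the term. But the article does describe the model's interactions and names only one, so a model run as written would use a single coefficient.

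Finally, the same algebra applies to baseline CAST. That is fair. The case is clearest for baseline joints, which is the outcome's own baseline value.

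**Conclusion.** The point holds as a minor improvement to the stated model, not as a demonstrated bias. Run as written, the model can mis-adjust the 12-month contrast when two conditions hold together: the arms differ at baseline, and the baseline association changes over follow-up.

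Within the protocol's own SD range and for chance imbalance, the error is small beside the planned gap. A larger share, such as a fifth or a quarter of the gap, needs further assumptions. For example, a 2-joint imbalance with coefficients 0.80, 0.65 and 0.45 and the first set of weights above gives 0.26 × 2 = 0.52 joints, or 23% of 2.25. But 2 joints is about four standard errors (2 / 0.49) at an SD of 5 for the whole trial. Such a figure should not be read as the expected size. The error would matter more if the true SD is well above 5, in the region-level analyses, or if recruitment has made the arms differ systematically.

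**What to change.** Add a baseline joints by time point interaction to the primary mixed model, with time point categorical in both this and the group interaction, and take the 12-month group contrast from that model. State this before the outcome data are examined, so that it is not a post-hoc choice. If the full analysis plan already has the term, a sentence saying so is enough.

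The cost is two degrees of freedom. No new data and no change to trial procedures are needed. In the simulations the term removed the conditional error, slightly improved precision when the coefficients decline, and left precision unchanged when they do not.

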**Methods:**

A randomized clustered controlled trial, stratified over three areas (Auvergne, Languedoc-Roussillon, and Rhône - Alpes), comparing an intervention group, which carries out the BI in consultation, and a control group, which ensures routine medical care. The main assessment criterion is the consumption of cannabis by amount of joints per month, at 12 months. The amount necessary to highlight a significant difference between the two groups of 30% of consumption at 12 months is 250 patients (50 GPs, 5 patients per GP; risk α = 5%; power = 90%; intra-cluster correlation coefficient ρ = 0.2; Hawthorne effect = 15%; lost to follow-up rates for GPs = 10% and for patients = 20%). This plan is replicated for the three areas, and therefore a total of 750 patients are expected.

The secondary criteria for judgment are the associated consumption of tobacco and alcohol, the perception of the consequences of consumption, and the driving of a vehicle following consumption.

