The authors hypothesize that in France, a BI in general medicine could enable identification of cannabis consumption in adolescents and propose early treatment, intended to reduce their consumption.

The main objective of the CANABIC study is to measure the effect at 12 months of a BI by GPs on cannabis consumption among recent user adolescents of 15 to 25 years of age. The secondary objectives relate to the variations in intermediate cannabis consumption at 3 and 6 months, variation in consumption associated with other methods of consumption (e.g., “bongs”), variations in consumption associated with alcohol and tobacco, the change in the perception of adolescents regarding the effects of their cannabis consumption on their personal, social, and professional lives, and on driving following the consumption of cannabis.

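### The secondary analysis compares drink-driving, but the declared outcome is driving after cannabis; the same incomplete sentence does not name tobacco and alcohol consumption

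*Protocol article*

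**What the plan says.** The secondary outcomes are declared in three places in the protocol article.

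- **Abstract, Methods.** "The secondary criteria for judgment are the associated consumption of tobacco and alcohol", followed by the perceived consequences of use and "the driving of a vehicle following consumption".
- **Background, last paragraph (objectives).** Among others, "variations in consumption associated with alcohol and tobacco", the change in how adolescents perceive the effects of their cannabis use, and an item "on driving following the consumption of cannabis".
- **Methods, opening section.** The GP records on case report forms at 3, 6 and 12 months the switch to other ways of using cannabis and "the impact of the change in cannabis use on tobacco and alcohol consumption". The patient questionnaire at the start and end of the study covers how cannabis is used and "changing perceptions of the danger of consumption for health, and driving after smoking".

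The Recruitment section adds that cigarette and alcohol consumption are recorded at the 3- and 6-month visits.

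The Statistical analyses section then lists what the random-effects secondary analyses will compare: method of consumption, supply method, perceived effects, and driving. The end of that list, with the driving item, reads "perception of the effects on health, professional life, social life, and driving under the influence of alcohol will be also compared". The next sentence says that these data come from the patient questionnaire.

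**The concern.** The substance changes between the objective and the analysis. Driving after cannabis and driving after alcohol are different behaviours, and only the first is an aim of this trial. Anyone who later compares the reported outcomes with the planned ones would see either a declared outcome without a planned analysis, or a reported outcome that was not the planned one. Both look like outcome switching, even if the cause is a slip of the pen.

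The second, weaker part is that the criterion the abstract names first, tobacco and alcohol consumption, is not in the analysis list. The Methods section makes the effect of changed cannabis use on these two substances a secondary hypothesis. It bears on how a fall in joints would be read, so readers would expect to find it beside the other secondary comparisons.

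**Working it through.** No figure in the plan depends on this point, so there is nothing to recompute. The check sets the outcome statements beside the analysis list.

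**Driving**

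| Place | Driving is tied to |
|---|---|
| Abstract, Methods | consumption (substance not named) |
| Background, objectives | cannabis |
| Methods, questionnaire items | smoking |
| Statistical analyses | alcohol |

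All three outcome statements fit driving after cannabis. The abstract leaves the substance open, but the consumption the trial studies is that of cannabis. The Background also gives accidents after smoking as part of the rationale. Alcohol is attached to driving in one place only, the analysis list. The wording in the Background and Methods could mean either the behaviour itself or the patient's perception of it. The mismatch is the same on both readings, because the substance there is still cannabis.

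**Tobacco and alcohol consumption**

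This criterion appears in all three outcome statements and in none of the items of the analysis list. Alcohol occurs in that list only inside the driving item.

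**Count against the abstract's secondary criteria**

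1. Tobacco and alcohol consumption: not in the list.
2. Perceived consequences of use: in the list.
3. Driving after consumption: in the list with a different substance.

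One of three matches, so 3 − 1 = 2 of 3 do not. If tobacco and alcohol are counted separately, there are four criteria, of which three do not match. The grouping in the abstract gives two of three, and that is the count used here.

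**The case against.** The strongest reply is that this is an obvious wording slip. The objectives and the questionnaire make the intent plain, and a drink-driving comparison would have no data to run on, since no such item is described as collected. The reply is fair as to intent and limits the harm. It does not make the sentence right: the sentence stands in the section that states the analysis, and no fuller document could bring it into agreement with the objectives.

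On tobacco and alcohol the reply is stronger. The sentence is damaged: its verb of comparison has lost its object, and its closing words suggest that the list is additional to something else. The next sentence ties the list to the questionnaire, so the list may cover questionnaire items only. An article may also leave the full set of secondary analyses to a fuller document. A reader might infer that tobacco and alcohol will go unanalysed, or that a shift to these substances will go untested. The documents do not support that. They declare these outcomes, provide for their collection, and nowhere say that they will not be compared. What stands is that the list does not match the criteria.

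Four further inferences also fail.

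- **Data source.** Attributing the listed data to the questionnaire is not an error on account of tobacco and alcohol, because these are not in the list. Methods draws the same line between case report form and questionnaire items.
- **Bongs.** Bong use is not missing. The list includes method of consumption, and Methods counts joints or bongs under how cannabis is used.
- **Supply method.** It is in no stated objective, but Recruitment describes the questionnaire's extra content in open terms, so comparing this item contradicts nothing.
- **Substitution.** Nothing in the article makes a shift to alcohol or tobacco the main way a fall in joints could be offset. Other ways of using cannabis are named alongside them.

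**Conclusion.** The driving mismatch holds with high confidence as a direct contradiction within the article: the analysis names a substance that no outcome statement supports. The tobacco and alcohol gap holds only as an incomplete list that should be brought into line with the declared criteria, and not as evidence that these outcomes were dropped. The point is minor, since only secondary outcomes are touched.

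The conclusion assumes that driving after consumption in the abstract and after smoking in Methods both mean cannabis, as the objectives say. It also assumes that the article describes every driving item that is collected. If the full questionnaire also asks about drink-driving, that comparison would have data, but the declared cannabis outcome would still lack a stated analysis.

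**What to change.** Rewrite the one sentence on secondary analyses in the Statistical analyses section:

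- Change the driving item to driving after cannabis consumption.
- Complete the sentence so that it names tobacco and alcohol consumption, from the case report forms at 3, 6 and 12 months, among the outcomes compared between groups with random-effects models.
- Keep the statement about the questionnaire for the questionnaire items only, so that adding the two case report form outcomes does not create a new inconsistency.

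The cost is one sentence. The article already provides for collecting the data, and no design parameter changes. The Trial status section describes the study as ongoing, so the wording can be settled before the results are analysed.
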